An increasing number of studies have examined different psychosocial interventions for cancer patients and their partners aimed at improving Quality of Life (QoL) and adjustment to the cancer diagnosis. Two systematic reviews with a total of 35 studies showed significantly small to moderate effect sizes regarding psychological, physical and relationship outcomes for both patients and partners (Regan et al. 2012; Badr & Krebs 2013). Nevertheless, the authors of both reviews pointed out that the results were influenced by conceptual and methodological limitations of the intervention studies, such as no specified theoretical framework, small sample sizes, high attrition rates and limited use of intention-to-treat analysis. The authors stated the need for well-designed studies that also investigate the integration of studies into clinical cancer care as well as cost-effectiveness. Furthermore, they stated that the content of an intervention should be flexible, hence making it possible to address couples’ present needs and to prepare patients and partners for psychological challenges they might experience later in the course of disease. A systematic review with 10 studies of psychological intervention for breast cancer patients and their partners (Brandao et al. 2014) concluded that these interventions appear to be effective, but these effects are influenced by similar limitations.

Based on the findings of previous research presented above, we developed a flexible intervention for couples facing breast cancer, addressing present psychosocial needs and helping to prepare for future challenges. Specifically, HiH is a psychological attachment-oriented couple intervention aimed to enhance dyadic adjustment through encouraging interdependent coping within the couples (e.g., discussing emotions and concerns and exchanging support). In turn, an interdependent coping style is expected to decrease symptoms of distress in initially distressed breast cancer patients and partners and to prevent distress in initially non-distressed breast cancer patients and partners. The remainder of this paper describes the theoretical framework and development of the HiH intervention and the design of the HiH RCT.

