### Randomisation

Randomisation was conducted following return of the signed informed consents and baseline questionnaires from patient and partner. Couples were randomised to the intervention or control group according to a computer-based randomisation procedure. The randomisation program was developed by a statistician of the research group and administered by an independent research assistant. The randomisation procedure was stratified on centres and each centre was block randomised in sequences calculated on the basis of each centre’s annual number of breast cancer surgeries. The block randomisation should ensure a more constant workload for the psychologists who had permanent positions in parallel with the project. All except the statistician were blinded to the block sizes and allocation sequence.

Couples were phoned by the project manager and informed about randomisation allocation. Obviously participants were not blinded with regard to the group assignment. Due to geographical reasons it was not possible to randomise the psychologists to centres.

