**Table 1 Tab1:** **Issues to address in hand in hand couple sessions**

Issues	Objective
Couples’ sense of attachment-related security	The couple is supported in focusing on their relationship strengths and attachment security, and supported in creating new emotional experiences
Level of individual emotional distress and needs	The couple is supported in verbalising their level of emotional distress and emotional needs, and feeling of attachment security
Knowledge of and experiences with cancer	The couple is supported in sharing their knowledge about breast cancer and their previous experiences with cancer, and how they influence their current situation
Psychological disorders	The couple is supported in verbalising present or previous psychological conditions, and if any, how they affect the couple in their current situation
Former stress-full life events	The couple is supported in verbalising previous experiences of emotional distress and their individual and dyadic adjustment in these distressed situations and how they can use these experiences in their current situation
Intimacy and sexual function	The couple is supported in verbalising needs and expectations related to intimacy and sexuality
Other stressors	The couple is supported in verbalising other factors that may affect the couple emotionally such as children’s and grandchildren’s reactions, work situation for them both, other diseases, economy and so forth

If couples randomised to the intervention group did not want to schedule the first session at their first contact with a psychologist, they could call back and schedule it within two months after randomisation.

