### Outcomes and data collection

Data were collected by questionnaires completed by patients and partners separately. Questionnaires and prepaid envelopes were mailed to patients and partners prior to randomisation (T1) and at the 5-month (T2) and 10-month (T3) follow-up.

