### Statistical methods

The primary outcome being change in breast cancer patients’ cancer-related distress between T1 and T2 will be analysed with a linear regression, adjusted for baseline. Secondary outcomes will be analysed by means of multilevel analysis. Secondary analysis will be performed for selected variables and the effect over time on distress will be analysed. Factors that can affect level of distress will be investigated and adjusted for. Data on patients and partners as individuals will be analysed with multilevel techniques. Modified ITT analysis will be performed with a clear description of exactly who was included in each analysis.

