Furthermore, the HiH intervention addressed both distressed and non-distressed breast cancer patients and partners. We planned an intervention addressing attachment security and promoting new emotional experiences in a safe environment. A limitation of our design is that we compared the HiH intervention in addition to usual care with usual care only. It may be difficult to interpret the results with regard to the effect of the intervention, because a possible effect may be due to the mere fact that the intervention makes it possible for the couple to benefit from having leisure time together in a stressful situation.

To enhance protocol adherence, we made a treatment fidelity checklist to measure if the session had been performed in compliance with the intervention guide.

Some patients and/or partners declined to participate, because they felt overwhelmed by their new life situation and ongoing treatment or did not have the time to participate. Therefore, our sample might not be representative of primary breast cancer patients and their partners in general. We will address this by comparing characteristics of participants and non-participants.

By December 2013, the HiH study had succeeded in including 199 couples. Our sample size of 220 couples was calculated with a 0.90 power. Due to the fact that the inclusion at Centre 3 was delayed, we redid the sample size calculation with a 0.80 power. Based on this calculation, we wanted to include 166 couples. To take into account a risk of attrition of 20% we included 199 couples.

To conclude, receiving attachment-oriented psychological counselling in the early treatment phase is expected to reduce distress and to improve dyadic adjustment and health-related quality of life in breast cancer patients and their partners. If proven effective, this intervention would be helpful in optimising psychosocial care and rehabilitation of couples coping with breast cancer.

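### Modified ITT is left undefined, and the primary T1–T2 regression cannot use patients without a T2 IES score unless values are imputed, although 20% attrition is allowed for and T3 scores exist

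*Protocol article*

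**What the plan says.** The only analysis set that the protocol article names is in its Statistical methods section: "Modified ITT analysis will be performed with a clear description of exactly who was included in each analysis". The modification is not defined there or elsewhere in the article.

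The same section says that the primary outcome, the change in the patient's IES between T1 and T2, "will be analysed with a linear regression, adjusted for baseline". For the rest it says: "Secondary outcomes will be analysed by means of multilevel analysis". It also plans to look at distress over time.

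Other places that bear on the point:

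- Discussion, on the size of the trial: "To take into account a risk of attrition of 20% we included 199 couples".
- Randomisation: "Obviously participants were not blinded with regard to the group assignment".
- Outcomes and data collection: "Data were collected by questionnaires completed by patients and partners separately". The questionnaires were sent by post.
- Potential covariates: outcomes were measured at all three time points apart from a short list of exceptions. IES is not among the exceptions, so a T3 score is collected.
- The paragraph after Table 1: intervention couples who did not book a first session at first contact could defer it, in that "they could call back and schedule it within two months after randomisation".
- Background: the review authors faulted earlier trials for "small sample sizes, high attrition rates and limited use of intention-to-treat analysis".

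**The concern.** Two choices act together. First, a modified ITT departs in some way from analysing everyone randomised in the allocated arm, and the article does not fix how. Failure to start sessions can occur only in the intervention arm, and nothing in the article rules out a modification that leaves non-starters out. Such a rule would act on one arm only.

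Second, a regression on change to a single follow-up time needs that follow-up value. A patient who returns T1 and T3 but not T2 gives information about her T2 score, and this model ignores it. Participants know their allocation and report their own outcome, so whether a questionnaire comes back could depend on arm and on how the patient feels. If it does, and baseline IES does not account for it, the primary contrast is biased. Even where there is no bias, precision is lost.

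**Working it through.** **Inputs.** From the Sample size section: relevant difference 7 IES points, SD 16.5, alpha 0.05. From the Discussion: 166 couples required at 0.80 power, 20% attrition, 199 included. Assumed because not stated: 1:1 allocation and a two-sided test.

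**1. The plan's attrition figure.** 166 × 1.20 = 199.2, which gives the stated 199. The trial was therefore sized on couples remaining after loss. (Whether 166 follows from an SD of 16.5, and whether multiplying by 1.20 is the right allowance, are separate questions that this point does not need.)

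**2. Patients outside the primary test if T2 loss reaches 20%.** 0.20 × 199 = 39.8, about 40. Remaining: 199 − 39.8 = 159.2, about 159, which is below the plan's own 166. The primary outcome is the patient's IES alone, so the unit lost is the patient without a T2 score, not the couple.

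**3. Precision.** Two-sample approximation with no gain from baseline adjustment: power = Φ(7 / (SD × √(4/N)) − 1.96).

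- N = 199, SD 16.5: standard error 2.339, 7/2.339 = 2.992, power 0.849.
- N = 159.2, SD 16.5: standard error 2.615, 7/2.615 = 2.676, power 0.763.

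Baseline adjustment would raise both. A longitudinal model would not restore the first figure. It recovers part of the gap, depending on how many patients miss T2 but return T3, and the documents do not give that number.

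**4. Bias (assumed values, not in the documents).** Let m be the proportion missing in an arm and D the amount by which missing patients' T2 scores exceed those of observed patients with the same baseline. The complete-case mean of that arm is too low by m × D. The error in the contrast (intervention minus control) is −(m_I × D_I) + (m_C × D_C).

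| Scenario | Shift in points | Share of 7 points |
|---|---|---|
| 20% missing in each arm, D = 4 in one arm, 0 in the other | 0.20 × 4 = 0.8 | 11% |
| 20% missing in each arm, D = 8 in one arm, 0 in the other | 0.20 × 8 = 1.6 | 23% |
| 25% and 15% missing, D = 7 in both arms | (0.25 − 0.15) × 7 = 0.7 | 10% |
| Same proportion and same D in both arms | 0 | 0% |

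In SD units the 4 to 8 points are 4/16.5 = 0.24 to 8/16.5 = 0.48. If the worse dropouts are in the intervention arm, the benefit is overstated. If they are in the control arm, it is understated.

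**The case against.** The article condenses a fuller plan. The exact definition of the analysis set and the handling of missing data usually sit in a statistical analysis plan, which is not shown. That stands, and it limits the point to what the article itself commits to: an analysis other than full ITT, and a single-time-point primary model.

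Several stronger readings are tempting and are not supported:

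- *That the population is chosen anew for each analysis.* The sentence promises to report who was included. Returns differ by scale and time point, and disclosing this is good practice.
- *That randomised couples are dropped.* No exclusion rule is given, and imputation is not ruled out.
- *That missed sessions or an absent partner remove the patient.* Attendance does not govern postal questionnaires that patient and partner complete separately.
- *That the trial contradicts its own standard.* The Background remark on limited ITT reports what review authors said. The limitations that the Discussion claims to overcome are small samples, large attrition, poor description of attrition and unspecific randomisation procedures. Limited ITT is not on that list, so the tension is mild.
- *That T3 is discarded altogether.* An analysis of distress over time is planned. T3 is absent only from the primary contrast.

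A baseline-adjusted regression is also valid when missingness depends only on arm and baseline IES, and the mixed model rests on missing-at-random too. Patients who leave after T1 add almost nothing to the T2 contrast under either model. All of this is fair. It makes the gain modest but does not remove it.

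**Conclusion.** The point holds in a limited form. The article commits to an undefined modified ITT and to a primary model that, without imputation, cannot use patients lacking a T2 IES. If T2 loss equals the 20% planning allowance, which the article does not tie to T2, about 40 of 199 patients would be outside the primary test. That is a scenario, not a documented exclusion.

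A reader might go further and infer that the primary result is biased by a known amount. The documents do not support that. Nothing says that return of questionnaires depends on arm, and the 0.8 to 1.6 points require informative loss in one arm only, beyond what baseline IES explains. With loss alike in both arms the shift is zero. What remains is a better and inexpensive analysis than the one stated, within the multilevel methods that the trial already plans to use. It is a change that should be made, with medium confidence.

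**What to change.** Before analysis, state the following in the plan:

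1. All randomised patients are analysed in their allocated arm, regardless of sessions attended. If any modification is kept, define it in advance.
2. The T2 contrast comes from a longitudinal mixed model of patient IES at T1, T2 and T3, with treatment by time, baseline constrained equal across arms, and centre.
3. The baseline-adjusted complete-case regression on T1–T2 change is kept as a sensitivity analysis.
4. A delta-shift analysis makes missing T2 scores worse, for example by 4 and 8 points in the intervention arm, to probe departures from missing-at-random. It cannot prove or refute that assumption.

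The cost is some wording and a little more programming. No new data are needed, because IES is already collected at T3. The downside is reliance on missing-at-random, and the gain comes mainly from patients who miss T2 but return T3.

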## Discussion

To our knowledge HiH is the first psychological attachment-oriented couple intervention, targeting both initially distressed and non-distressed breast cancer patients and partners, that has been tested in a randomised controlled trial setting. Moreover, the focus on interdependent coping in the early treatment phase is a unique aspect. Conversely to other psychological interventions for patients and partners facing breast cancer, the HiH intervention used a semi-structured protocol, allowing adjustment of the intervention with regard to the number and content of the sessions.

We developed an intervention for couples who are distressed in the early breast cancer trajectory and non-distressed couples who may become distressed during the breast cancer trajectory. The aim was to reduce distress. The number of 4 to 8 sessions was estimated to be adequate to help couples to gain attachment security and to create new emotional experiences, thereby reducing and preventing distress.

Furthermore, we know that usual care varies across centres. However, we took great care to ask all participants at T3 if they had received any additional support and counselling (other than the intervention), and by whom this support has been provided. This information will be helpful in the interpretation of the results.

We have included therapeutic alliance and attachment-related anxiety and avoidance as potential covariates. Thereby we can ascertain potential moderating effects in the relationship between the participants and the psychologists. The measure of attachment-related anxiety and avoidance can help us to understand, if for example patients high on attachment-related anxiety benefit more from the intervention compared to patients low on attachment-related anxiety.

Results from previous intervention studies of breast cancer patients and their partners have been substantially influenced by methodological limitations such as small sample sizes, large attrition rates, inadequate description of attrition rates, and lack of specific randomisation procedures (Regan et al. 2012; Badr & Krebs 2013). We took the challenge to design and conduct a multi-centre, randomised, controlled trial that overcomes these limitations.

Furthermore, the HiH intervention addressed both distressed and non-distressed breast cancer patients and partners. We planned an intervention addressing attachment security and promoting new emotional experiences in a safe environment. A limitation of our design is that we compared the HiH intervention in addition to usual care with usual care only. It may be difficult to interpret the results with regard to the effect of the intervention, because a possible effect may be due to the mere fact that the intervention makes it possible for the couple to benefit from having leisure time together in a stressful situation.

To enhance protocol adherence, we made a treatment fidelity checklist to measure if the session had been performed in compliance with the intervention guide.

Some patients and/or partners declined to participate, because they felt overwhelmed by their new life situation and ongoing treatment or did not have the time to participate. Therefore, our sample might not be representative of primary breast cancer patients and their partners in general. We will address this by comparing characteristics of participants and non-participants.

By December 2013, the HiH study had succeeded in including 199 couples. Our sample size of 220 couples was calculated with a 0.90 power. Due to the fact that the inclusion at Centre 3 was delayed, we redid the sample size calculation with a 0.80 power. Based on this calculation, we wanted to include 166 couples. To take into account a risk of attrition of 20% we included 199 couples.

To conclude, receiving attachment-oriented psychological counselling in the early treatment phase is expected to reduce distress and to improve dyadic adjustment and health-related quality of life in breast cancer patients and their partners. If proven effective, this intervention would be helpful in optimising psychosocial care and rehabilitation of couples coping with breast cancer.

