### Sample size

Values of cancer-related distress on the Impact of Event Scale (IES–Total) range from 0 to 75. Based on prior intervention studies of breast cancer patients and their partners using IES–Total (Scott et al. 2004; Manne et al. 2005b), we estimated the mean of the patients to be 27 at baseline with a standard deviation (SD) of 16.5. Congruous to these previous studies, we considered a difference of 7 points clinically relevant. With a power of 0.90 and an alpha of 0.05, we aimed to include 220 couples.

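### The 20% attrition allowance multiplies 166 by 1.2 instead of dividing by 0.80, so 199 couples cover only 16.6% attrition; separately, 166 and 220 do not follow from the stated SD of 16.5

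*Protocol article*

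**What the plan says.** The Sample size section of the protocol article plans on the patients' total Impact of Event Scale score. It says "we estimated the mean of the patients to be 27 at baseline with a standard deviation (SD) of 16.5" and "we considered a difference of 7 points clinically relevant". The target follows: "With a power of 0.90 and an alpha of 0.05, we aimed to include 220 couples". It mentions no attrition allowance.

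The Discussion reports the revision. After a delay at one centre, "we redid the sample size calculation with a 0.80 power". It continues: "Based on this calculation, we wanted to include 166 couples". The final number is then explained: "To take into account a risk of attrition of 20% we included 199 couples". No inflation formula is given.

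Under Statistical methods, the primary outcome (change from baseline to the 5-month follow-up) is to be analysed by linear regression adjusted for baseline. No baseline-to-follow-up correlation, sidedness of alpha or allocation ratio is stated.

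**The concern.** An attrition allowance is meant to leave the required number in the analysis after the expected loss. Attrition removes a share of those enrolled, so the required number is divided by one minus the loss rate. Multiplying it by one plus the loss rate gives too few. The three figures in the Discussion (166, 20% and 199) fit the second operation.

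This is the only justification in the article for the number actually enrolled. A reader of a non-significant primary result would credit the trial with 0.80 power after a 20% loss, and the article's own figures do not quite support that. Checking the base number of 166 also shows that it does not follow from the planning SD printed in the Sample size section.

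**Working it through.** **Inputs.** From the Sample size section: SD 16.5, difference 7, alpha 0.05, and 220 couples at power 0.90. From the Discussion: 166 couples at power 0.80, 20% attrition, 199 included. Assumed because not stated: two-sided alpha and 1:1 allocation.

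**1. The allowance.**
- Reproducing the article's figure: 166 × (1 + 0.20) = 199.2, reported as 199.
- Correct inflation: 166/(1 − 0.20) = 207.5, so 208 couples, 9 more than 199.
- Couples left after a 20% loss from 199: 199 × 0.80 = 159.2, so 159, which is 7 below 166.
- Largest loss that still leaves 166: 1 − 166/199 = 0.166, or 16.6%.

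This step needs no assumption about SD, sidedness or allocation.

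**2. The base number.** Normal-approximation formula, per group: n = 2 × [(z for alpha/2 + z for power) × SD / difference]².

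| SD | Power | n per group | Couples in total |
|---|---|---|---|
| 16.5 (stated) | 0.80 | 87.2, so 88 | 176 |
| 16.5 (stated) | 0.90 | 116.8, so 117 | 234 |
| 16.0 (not in the article) | 0.80 | 82.01, so 83 | 166 |
| 16.0 (not in the article) | 0.90 | 109.8, so 110 | 220 |

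The noncentral t adds a couple or two at SD 16.5 (234 couples give 0.898 and 236 give 0.901), hence about 176 and 235. One-sided testing does not explain the gap: at SD 16.5 it gives 138 and 192. An SD of 16.0 reproduces both 166 and 220. It is a back-solved value.

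**3. Unadjusted power.** Noncentral t with total N, noncentrality = 7/(SD × √(4/N)) and N − 2 degrees of freedom.

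| Evaluable couples | SD 16.0 | SD 16.5 |
|---|---|---|
| 166 | 0.800 | 0.776 |
| 159 | 0.783 | 0.758 |

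Reading down a column gives the cost of the attrition slip: 0.017 at SD 16.0 and 0.018 at SD 16.5. Reading across gives the cost of the SD mismatch: about 0.025. The full distance from 0.800 to 0.758 is the sum of the two. Correct inflation to 208, leaving 166 evaluable, would still give only 0.776 at the stated SD.

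The difference detectable at 0.80 power divides in the same way. At SD 16.5 it is 7.22 points with 166 couples and 7.38 with 159, so most of the excess over 7 is there before any attrition. At SD 16.0 with 159 couples it is 7.15.

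**4. Power under the planned baseline adjustment.** Residual SD = 16.5 × √(1 − r²), 159 couples. The correlation r is an assumption.

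| r | Residual SD | Power |
|---|---|---|
| 0 | 16.50 | 0.758 |
| 0.25 | 15.98 | 0.784 |
| 0.32 | 15.63 | 0.801 |
| 0.50 | 14.29 | 0.866 |

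**The case against.** The strongest reply is that the consequence is slight. Taken alone, the slip costs under 2 points of power. Recruitment is over, 20% is a planning risk and not an observed loss, and no analysis changes. The planned regression also adjusts for baseline, so with a correlation of about 0.32 or more 159 couples would reach 0.80 even at SD 16.5. All of this stands, and it limits the severity. It does not remove the error: the article says that 199 allows for 20% attrition, and 199 does not. The article states no correlation and takes no credit for adjustment, so adjustment cannot be read as the reason for the number.

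Four stronger readings are tempting, and the document does not support them:

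- **That the attrition slip lowers power to 0.76 and raises the detectable difference to 7.4 points.** More than half of each departure comes from the mismatch between SD 16.5 and 166, and exists before any couple is lost.
- **That the trial misses 0.80 power.** This holds only for an unadjusted comparison. For the planned analysis, power may lie on either side of 0.80, depending on a correlation that is not given.
- **That the earlier target of 220 was misdescribed because a 20% loss would cut its power.** The article says "Our sample size of 220 couples was calculated with a 0.90 power". It never claims 0.90 power after attrition, so there is no such claim to rebut.
- **That the slip contradicts "We took the challenge to design and conduct a multi-centre, randomised, controlled trial that overcomes these limitations".** That sentence concerns small samples, large attrition, poor description of attrition and unspecific randomisation procedures in earlier studies. A shortfall of 9 couples in a planning allowance does not falsify it.

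**Conclusion.** The statement about attrition is wrong as written. On the article's own figures, 199 couples protect 166 only up to 16.6% attrition, a 20% loss leaves 159, and 208 would have been needed. That part is plain arithmetic.

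The power consequence is modest. It is about 0.78 instead of 0.80 if 166 is accepted as the 0.80 requirement, which corresponds to an SD of 16.0 that the article does not state. On the stated SD of 16.5 it is about 0.76, and there the larger part of the shortfall comes from 166 not following from the stated inputs. These powers assume a two-sided 0.05 test, 1:1 allocation and no baseline adjustment. Severity is minor to moderate: the justification of the sample size needs correcting, but the design and analysis do not.

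**What to change.** Three changes of wording, all in the sample size justification:

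1. State that 199 couples allow for 16.6% attrition, and that 20% attrition would leave 159 couples with unadjusted power of about 0.78 (SD 16.0) or 0.76 (SD 16.5).
2. Reconcile the stated SD of 16.5 with 166 and 220. Either give the SD or other assumption that was used, or report the numbers that SD 16.5 implies (about 176 and 235). State sidedness and allocation ratio at the same place.
3. Add power under the planned baseline-adjusted regression over an assumed correlation range. For 159 couples at SD 16.5 this is 0.78 at r = 0.25, 0.80 at about r = 0.32 and 0.87 at r = 0.50.

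The cost is a few sentences and a slightly less favourable unadjusted power figure. No further couples are needed.
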